## Abstract

**Abstract:**

**Introduction:**

Acute uncomplicated urinary tract infection (UTI) is a common condition with potentially serious sequelae that is mostly diagnosed and managed in primary care settings. Around half of all women have a UTI in their lifetime, and a quarter experience an infection caused by organisms resistant to more than one antibiotic. Reducing inappropriate prescribing of antibiotics is a core tenet of antimicrobial stewardship. However, current diagnostics for UTI are unfit for purpose in acute (highest prescribing) settings, being too slow to inform the required immediate decision-making and often confounded by sample contamination.

Rapid point-of-care diagnostic tests (POCTs) that facilitate timely decision-making are potential solutions to this problem. Several such tests have reached advanced stages of technology readiness, but their diagnostic performance has not been evaluated in primary care with clinical users. To progress novel tests towards implementation, a diagnostic field study is required, to allow for parallel and sequential evaluation of multiple tests in a primary care population.

**Methods and analysis:**

We will recruit participants assigned female at birth from primary care clinics in England who contact their clinic with symptoms of acute uncomplicated UTI. Eligible participants will complete a short questionnaire to capture symptoms and symptom severity and will provide a urine sample. Samples will be split and initially tested using novel index tests (POCTs) and conventional urinalysis ‘dipstick’ at the primary care clinic. The second part of the sample will be processed at a National Health Service-based reference laboratory using a modified reference standard including microscopy, microbiological culture, pathogen speciation and antimicrobial susceptibility testing. The UTI reference standard culture, although based on the national methods, is modified to provide accurate bacterial counts, better to define a microbiological diagnosis of UTI. Susceptibility testing will be performed using ‘gold-standard’ methods, not usually performed in diagnostic laboratories. The primary outcome will be the diagnostic performance (sensitivity, specificity, positive and negative predictive values) of POCTs for detection of UTI and antimicrobial susceptibility for POCTs that include antimicrobial susceptibility testing. Secondary outcomes will include the symptom profile of patients presenting with uncomplicated UTI, a theoretical determination of how use of POCT results might change prescribing, an understanding of POCT failure rate and qualitative capture of the experiences of those using the POCT to deliver the study in primary care clinics.

**Ethics and dissemination:**

Ethical approval was received from the London Central Research Ethics Committee (23/LO/0371) and the UK Health Research Authority. We will publish the findings of The plaTform fOr Urinary tract infection diagnostiC evAluatioN evaluations in peer-reviewed medical journals and more broadly following a dissemination plan formulated by a communications specialist in consultation with patients and the public.

**Trial registration number:**

ISRCTN80937472.

STRENGTHS AND LIMITATIONS OF THIS STUDYProspective study design.Common sample used for (potentially) multiple index point-of-care tests (POCTs) and reference standard testing.Embedded qualitative study to capture clinical user perspectives on test use and implementation.Limited power to determine the diagnostic performance of POCTs that include antimicrobial susceptibility testing against all potential antibiotics included on POCT testing panels, due to low prevalence of organisms resistant to antibiotics such as nitrofurantoin.The modified urinary tract infection reference standard culture (as performed by the National Health Service-based reference laboratory), while being modified for improved accuracy still has limitations which may make interpretation of discordant results challenging—conducting multiple POCT simultaneously may help mitigate this.

## Introduction

 Half of all women experience a urinary tract infection (UTI) in their lifetime.^1^ The reference standard test for UTI is laboratory microscopy, microbiological culture and antimicrobial susceptibility testing (AST). This process typically takes 2–3 days and may not produce clinically useful information; up to 30% of samples can be contaminated by host flora^2^ and loss of bacterial viability or overgrowth with time can yield misleading or no results. Use of sample collection tubes containing boric acid mitigates against bacterial overgrowth, but use of these tubes has not been universally adopted by laboratories. In consequence, the majority of suspected infections encountered in primary care are identified and treated empirically using clinical criteria, which have limited sensitivity and specificity.^3^

Antimicrobial resistance is one of the greatest threats to human health and is driven further by inappropriate prescriptions of antibiotics.^4^ Our study of patients with microbiologically confirmed UTI in four EU member states detected urinary pathogens with resistance to a single antibiotic in 27% (57/209) of patients and resistance to >1 antibiotic in 25% of patients (53/209).^5^ Therefore, there is pressure to reduce inappropriate (unnecessary or incorrect) antibiotic prescribing for UTI, while acknowledging that undertreatment has the potential to lead to serious sequelae.^6^ The current standard of care involves using a combination of symptoms, signs and simple dipstick results to predict which women are most likely to have infection.^7^ Better tests are required to help clinicians avoid prescribing antibiotics in women who do not need them and prescribe the correct antibiotics to those who do.

Rapid point-of-care diagnostic tests (POCTs) are potential solutions to this problem. A survey of 1109 UK general practitioners (GPs) in 2012 highlighted UTI as the condition for which a POCT would be most helpful to support diagnosis.^8^ Current POCTs for UTI are suboptimal, with urine dipsticks neither sensitive nor specific enough^9^ and are unable to provide information on the antibiotic susceptibility of pathogens. Diagnostic tests based on point-of-care bacterial culture on solid media are available, but these incorporate a 12–24 hour incubation step and are therefore too slow to influence immediate decision-making, and a trial incorporating this approach showed minimal impact on appropriate antibiotic prescribing.^10^ Thus, improved and more rapid POCTs are needed.

New technologies are aiming to deliver a rapid diagnosis and, in some cases, a uropathogen AST at the point-of-care, facilitating timely and targeted treatment. Although a number of developers have carried out laboratory evaluation work using bacterial cultures, urine samples ‘spiked’ with known uropathogens, and genuine patient samples, there have been no robust independent evaluations of these exciting technologies in real-world settings. It is vital that the performance of these diagnostic tests is evaluated before these devices are considered for inclusion in interventional studies or clinical practice.

In addition to POCT technologies, which are at or close to clinical readiness and so fully powered evaluations are appropriate, there are a number of innovators with potentially transformative early-stage technologies that require crucial proof of principle evidence, using fresh urine samples, to proceed further with development. Under these circumstances, we intend to nest small pilot studies alongside our full-scale evaluations. New POCTs will be introduced into this platform study as and when available.

## Methods and analysis

### Study design and setting

The plaTform fOr Urinary tract infection diagnostiC evAluatioN (TOUCAN) is a prospective diagnostic accuracy study allowing for parallel evaluation of index POCTs (referred to henceforth as POCTs) in a consecutively enrolled primary care population of female patients ≥18 years of age presenting with symptoms of uncomplicated UTI. TOUCAN began recruitment in September 2023. New POCTs will be introduced into the study as and when they become available, following due consideration of recruitment timelines to reach sample size. Participants recruited from primary care clinics in England will be asked to provide a single urine sample which will undergo analysis by POCTs at the point-of-care alongside conventional urinalysis dipstick test, then reference standard laboratory urine processing including microscopy, modified culture and AST (performed using ‘gold standard’ methods) at the National Health Service (NHS)-based reference laboratory. Participants will provide the urine sample at baseline (the day they consult healthcare) and answer a short questionnaire including their age, ethnicity, symptoms and confirmation of eligibility criteria. There will be no further patient follow-up, as this is a diagnostic accuracy study not concerned with effect on participant outcomes. Given the observational nature of the study, and uncertainty about test accuracy at this stage, POCT results will not be shared with participants or used to support clinical decision-making.

### Primary objective

To determine the diagnostic performance in a primary care field study of novel POCTs for diagnosing UTI against standard microbiology laboratory processing, including ‘gold-standard’ AST results. The reference standard for the study will conform to the definitions of UTI detailed in the UK Health Security Agency guide on the investigation of urine^11^ to determine microbiological diagnosis of UTI, while antimicrobial susceptibilities will be assessed in accordance with the International Standard 20776-1.^12^ Outcome measures will include sensitivity, specificity, predictive values and likelihood ratios for the detection of UTI and for AST results where this is an element of the POCT.

### Secondary objectives

To record the different symptoms of people who seek help from their GP with suspected uncomplicated UTI.Understand whether and how using the results of a new POCT would result in changes in antibiotic prescribing.Determine how often POCTs fail, and how frequently they give uninterpretable results.To explore the experiences and perceptions of primary care staff involved in the use of new POCT for UTI, and how these might affect the feasibility of future implementation.

### Study participants and their selection

People assigned female at birth, aged 18 years and over, presenting to primary care with suspected uncomplicated UTI will be eligible for participation in the study. The inclusion criteria detailed in box 1 are broad in order to encompass the widest range of inclusion criteria scenarios detailed across multiple manufacturers’ intended use statements.

Box 1Study inclusion and exclusion criteriaInclusion criteriaFemale* (including pregnant women).Aged ≥18 years.Presenting to UK primary care with current symptoms that have been present for fewer than 7 days, that the patient or their primary care health professional considers are consistent with an uncomplicated UTI.Clinician confirms that urine sample for analysis is useful for patient’s care.**Participant is willing to give consent for participation in the study.Exclusion criteriaPreviously recruited to this study.Unable to provide a sample that was taken within the timeframe specified by POCT developers.Unable to understand and complete trial materials in English.*Participants will be included only if they were assigned female at birth.**For example, urine sample tested before antibiotics are started to guide decision to prescribe and nature of prescription, or sample tested where UTI symptoms have persisted despite antibiotics to guide decision to prescribe and nature of prescription.POCT, point-of-care test; UTI, urinary tract infection.

### Recruitment

Study sites will be selected with the help of the National Institute for Health and Care Research Clinical Research Network and will consist of primary care practices that are willing and able to adhere to the requirements of the study protocol. Participants will be selected through participating practices and will be identified through two key routes:

When they book and attend (in person or on the telephone) a clinical appointment for a suspected, uncomplicated UTI.When they submit a urine sample for testing for a suspected, uncomplicated UTI at their primary care practice.

Potential participants who call the practice and state they have a possible UTI will be asked to come to the practice to provide a sample, once at the practice they will be asked if they are happy to take part in the study and if they indicate they are, the recruitment process described below will be followed.

### Screening and eligibility assessment

This will be a prospective opportunistic-recruitment study. Sequential potential participants will be screened as and when they present to their primary care practice with a suspected UTI. Once the participant has read the participant information sheet (PIS), signed the participant summary sheet (PSS) to indicate their consent and completed the baseline questionnaire, their responses to the eligibility questions will be assessed and confirmed by the member of the practice team who will run the tests. Relevant sections of the participant’s medical records will be reviewed by an authorised member of practice staff and any medical conditions relevant to the performance of the POCTs will be recorded in the study database. Potential participants should either receive the PIS in person at the practice, or they can be sent a link via text message by the GP to the trial website where they should download the PIS before they attend the practice. Once they attend the practice to produce their urine sample they will be presented with the PSS/consent form to sign.

### Informed consent

Online or written versions of the PIS will be presented to the participants detailing no less than: the exact nature of the study; what it will involve for the participant; the implications and constraints of the protocol; the known side effects and any risks involved in taking part. As all patient data will be collected at the baseline visit, it will not be possible to withdraw data and samples from the study after the baseline assessments are completed. This will be clearly explained in the PIS. Potential participants will be given time to consider the information, and the opportunity to question the Investigator, their GP or other independent parties to decide whether they will participate in the study. If they agree, consent proportionate to the study type and risk will be given by the participant signing and dating the appropriate part of the PSS/consent form. Study sites will use a web-based database system to record eligibility and confirm participant entry into the study, prior to the samples being processed for research.

### Data collection

The study will use a bespoke study database with eligibility screening, symptom questionnaire, baseline assessment, POCT and laboratory electronic case report forms (eCRFs) developed on the REDCap electronic data capture tools platform^13 14^ and hosted by the University of Oxford.

### Baseline assessments

Following participant consent and urine sample provision, the baseline questionnaire will capture the following information:

Whether the participant has previously taken part in the study.Duration of symptoms of the current episode.Participant age, affirmation of female gender assignment at birth and ethnicity.Date and time that urine sample was taken.Symptom severity of the following symptoms on a scale from 0 to 6, where 0 is ‘not affected’ and 6 is ‘as bad as it could be’: Fever, pain or burning when passing urine, increased urgency of urination, increased day and night time frequency of urination.Pregnancy status.Whether the patient suffers from recurrent UTIs.Whether the participant has taken antibiotics in the last 7 days and if so what antibiotics were taken.

Additional information on participants will be collected through a review of each participant’s medical notes by site staff to enable alignment of primary data analysis with the specific inclusion and exclusion criteria defined in POCT manufacturer instructions for use (IFU) documentation, including:

Any anatomical or functional abnormalities of the urinary tract.Presence of any indwelling urinary catheters.Whether the participant intermittently self-catheterises.Diagnosis of renal disease.If the participant is classified as immunocompromised according to the following definition: inherited immune disorders; undergoing treatment for cancer; history of haematological malignancy; HIV at all stages; receiving biologics, azathioprine, 6-MP, methotrexate, or ciclosporin; receiving steroids >20 mg/day or less in combination with other immunosuppressive therapies.Diagnosis of diabetes.

The member of staff processing the sample will confirm eligibility of the participant (that the participant is aged 18 or over, female, they have not taken part in the study before and have not had UTI symptoms for longer than 6 days) before they process the sample.

The following information will be collected by site staff during the visit and entered into the eCRF:

Time that each POCT and dipstick test was performed.Confirmation from a healthcare professional that a urine sample for analysis is useful for patient care.Whether an antibiotic has been prescribed for this suspected UTI episode, and if so, the class, dose and duration of the antibiotic (this may not be immediately known but will be recorded once known).Results from the POCTs and dipstick tests.Confirmation and date that a sample was sent to the study reference laboratory.

The following information will be collected by staff at the NHS-based reference laboratory and entered into the reference laboratory eCRF:

Reference test results.Sample tracking details, including date and time the sample was received at the laboratory.

As patients would normally provide a urine sample as part of standard care, the study does not use any additional interventions that could be considered to carry a risk to participants and so adverse event data will not be collected.

### Sample provision and handling, POCT(s) and reference standard

#### Sample provision and handling

Every participant will provide a midstream urine sample to their practice in a standard 30 mL universal container which does not contain sodium borate (Sterilin Polystyrene Universal, ThermoFisher Scientific, UK). Either fresh or previously collected samples will be used provided that they are processed within the time frame specified by the manufacturer of the POCT, but a fresh sample will be preferred if the participant is willing to provide one. POCTs will be carried out by a member of the practice team who has received training on the devices from the manufacturer—that is, mimicking as closely as possible how the test would be used in ‘real life’ primary care. If a sample is required for local laboratory testing as part of clinical management, the urine sample provided by the participant will be split using a no-touch technique. The fraction required by the local laboratory will continue to be processed as a standard clinical sample using routine NHS processes.

The fraction of the sample required for the study reference standard testing will then be sent to the NHS-based reference laboratory in a 30 mL sodium borate container (Sterilin Polystyrene Universal Boric Acid, Thermofisher Scientific, UK). All samples will be destroyed after all laboratory tests have been performed, although bacterial isolates will be retained.

### Index tests

Index tests will be POCTs for UTI, which may incorporate phenotypic AST or molecular determination of uropathogen resistance to antibiotics. Specific details of study POCTs will be included as protocol appendices, with amendments to the protocol and ethical approval concluded prior to introduction of new tests.

POCTs included in the protocol appendix of the application for ethical review were the Sysmex PA-100 AST System (Sysmex Astrego AB, Uppsala, Sweden)^15^ and the Lodestar DX with UTI test panel (Llusern Scientific, Cardiff, UK).^16^ Both technologies were included in the UK National Institute for Health and Care Excellence Health Technology Evaluation HTE7 ‘POCTs for UTIs to improve antimicrobial prescribing: early value assessment’, which recommended further clinical evidence generation prior to reconsideration of these tests for use. The Sysmex PA-100 AST POCT is an instrument-based assay with a disposable panel for the diagnosis of UTI and phenotypic AST directly from patient urine samples. The PA-100 AST determines bacteriuria within approximately 15 min against a cut-off value of 5×10^4^ colony-forming units (CFU)/mL; if bacteriuria is detected, the analyser continues to determine antimicrobial susceptibility of uropathogens against a panel of antibiotics including amoxicillin-clavulanic acid, ciprofloxacin, fosfomycin, nitrofurantoin and trimethoprim, with the AST step taking approximately 15–30 min. The Llusern Scientific POCT is an instrument-based assay for the loop-mediated isothermal amplification detection of clinically relevant levels of a panel of uropathogens directly from patient urine samples through detection of uropathogen DNA. Target uropathogens include *Escherichia coli*, Enterococcus spp., *Staphylococcus saprophyticus*, *Pseuodomonas aeruginosa*, *Proteus mirabilis* and Klebsiella spp., with the assay taking 40 min to complete following assay initiation. Additional tests may be added beyond those described in this paragraph.

POCT manufacturers will provide training on device use either in person or via video link directly to study sites and to members of the TOUCAN central trial team. Study sites will be asked to adhere to manufacturer prescribed Quality Control schedules and procedures, with instruction provided during device training and through associated instrument manuals.

### Conventional urinalysis (dipstick)

Sites will be provided with 10-parameter urinalysis reagent test strips (RS10, SureScreen Diagnostics, Annesley, UK), incorporating nitrite and leukocyturia detection. This test will be conducted concurrently with POCT runs and interpreted blind to any POCT results. The diagnostic performance of the urine dipstick in relation to the NHS-based reference laboratory result will be assessed and also compared with the diagnostic performance of POCTs. Clinicians caring for the patient will have access to the dipstick test result, which may help direct care.

### Laboratory reference standard

Reference testing will be conducted at the laboratory of the Specialist Antimicrobial Chemotherapy Unit, Public Health Wales. All urine samples will undergo automated microscopy using a Sysmex UF 5000 system, then 50 µL spiral plated onto UTI chromogenic media (diluted according to opacity of urine) and incubated overnight. Bacterial growth will be assessed as pure or predominant uropathogen growth and quantified to CFUs per mL (CFU/mL). Each significant uropathogen will be identified using the MALDI-ToF mass spectrometry method. The UTI definitions set out in the UK Health Security Agency (Public Health England at time of publication) guide on investigation of urine (B41)^11^ will be used for microbiological UTI diagnosis as primary reference standard. The guide defines UTI as either probable or possible UTI according to the following criteria: Probable UTI is defined as ≥10^5^ CFU per millilitre (CFU/mL) of pure culture, irrespective of white blood cell (WBC) levels. Possible UTI is defined using the following criteria: reculture at ≥10^5^ with predominant growth (where the second or third organisms are at least 3×log_2_ CFU/mL below the predominant organism) irrespective of WBC, growth of 2 organisms (dual culture: where both are ≥10^5^ or one is ≥10^5^ and the other ≥10^4^) accompanied by WBC, pure or predominant culture at 10^4^–10^5^ accompanied WBC, predominant culture at 10^4^–10^5^ of a UTI pathogen species accompanied by WBC OR pure or dual culture (where both present are known urinary pathogens at 10^3^–10^4^ accompanied by WBC).

Quantitative culture will allow the application of European Guideline thresholds (≥10^3^ CFU/mL) or similar if appropriate or desired. Antimicrobial susceptibilities will be performed by broth microdilution, the ‘gold-standard’ method, according to the International Standard 20776-1.^12^ Susceptibility to a panel of antibiotics, according to pathogen, will be tested, for example, ampicillin, cefoxitin, cefpodoxime, ciprofloxacin, clindamycin, co-amoxiclav, fosfomycin, nitrofurantoin, penicillin, pivmecillinam, teicoplanin, trimethoprim and vancomycin. Bacterial isolates will be stored at −80°C for further analysis.

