If feasible, for participants whose samples have been tested with more than one comparable POCT (ie, paired sampling), results from the different POCTs will be additionally cross-tabulated against each other. The number of participants prescribed discordant antibiotics will be tabulated and expressed as a proportion of the total, with a 95% CI. These will also be tabulated by the reason for the discordance—for example, an antibiotic prescription without confirmed UTI, or a specific antibiotic being prescribed to an individual for whom the organism was not susceptible to that antibiotic. An exploratory analysis will summarise the baseline symptoms and dipstick results of (1) participants for whom the POCT and laboratory reference test gave discrepant results and (2) participants for whom discordant antibiotic prescriptions were issued. If there are sufficient samples with multiple POCT results available, we will investigate using latent variable methods to simultaneously take account of all results performed on the same sample and quantify any changes of estimates in diagnostic accuracy parameters.^17^

The primary analysis for each POCT assessed will be based on participants’ compatibility with the exclusions of the relevant manufacturer’s IFU and associated Approved Documentation, and a sensitivity analysis will include all participants. The primary analysis will use the laboratory reference standard definition of probable UTI as defined in the details of the reference standard and a sensitivity analysis will use the definition of possible UTI. Another sensitivity analysis will exclude samples detected by laboratory culture to be positive for bacterial species as either the sole or the predominant species where the POCT does not test for this organism. Further sensitivity analyses will be prespecified in the statistical analysis plan.

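### As printed, the possible-UTI criteria drop two-pathogen cultures at 10^4–10^5 CFU/mL that they accept at lower and at higher counts; only the possible-UTI sensitivity analysis is affected

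*Protocol article*

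**What the plan says.** The Laboratory reference standard section takes its definitions from a national guide and prints them. "Probable UTI is defined as ≥10^5^ CFU per millilitre (CFU/mL) of pure culture, irrespective of white blood cell (WBC) levels", so a two-organism culture can never be probable UTI. The possible-UTI entries that bear on two organisms are:

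- at 10^5 or above, predominant growth regardless of white cells, with predominance defined as "where the second or third organisms are at least 3×log_2_ CFU/mL below the predominant organism";
- for two organisms at the higher counts, "growth of 2 organisms (dual culture: where both are ≥10^5^ or one is ≥10^5^ and the other ≥10^4^) accompanied by WBC";
- for the middle band, a first entry that reads "pure or predominant culture at 10^4^–10^5^ accompanied WBC";
- for the same band, a second entry that reads "predominant culture at 10^4^–10^5^ of a UTI pathogen species accompanied by WBC";
- for the lowest band, "pure or dual culture (where both present are known urinary pathogens at 10^3^–10^4^ accompanied by WBC".

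Under Statistical methods, the primary analysis uses probable UTI and "a sensitivity analysis will use the definition of possible UTI". Under Index tests, the PA-100 is described as calling bacteriuria against a cut-off of 5×10^4 CFU/mL.

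**The concern.** A rule that classifies infection by bacterial count should not withdraw infection status when the count rises and everything else stays the same. Read entry by entry, this one does. Two known urinary pathogens with white cells qualify in the lowest band, fail in the middle band unless one predominates, and qualify again once one reaches 10^5.

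The middle band also carries two entries where one would do. The second (predominant growth of a urinary pathogen) is wholly contained in the first (pure or predominant growth), so it adds nothing. It sits in exactly the band where an entry for two organisms is absent.

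The possible-UTI analysis is the article's check on a strict primary definition that needs pure growth at 10^5 or more. In that check, a test that correctly finds two pathogens in the middle band would be charged with a false positive. The PA-100 cut-off lies inside the band.

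**Working it through.** The article gives no figure to reproduce; the check is to apply the printed rule.

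**Inputs** (all from Laboratory reference standard): the possible-UTI entries above; two known urinary pathogens; white cells present; predominance read as three doublings, 2^3 = 8-fold.

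**Step 1: classify pairs of counts (CFU/mL).**

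| Higher | Lower | Ratio | Entry met |
|---|---|---|---|
| 5×10^3 | 5×10^3 | 1 | two pathogens at 10^3–10^4 |
| 2×10^4 | 5×10^3 | 4 | none |
| 2×10^4 | 2×10^4 | 1 | none |
| 5×10^4 | 5×10^4 | 1 | none |
| 9×10^4 | 2×10^4 | 4.5 | none |
| 9×10^4 | 1.1×10^4 | 8.2 | predominant at 10^4–10^5 |
| 2×10^5 | 3×10^4 | 6.7 | dual, one at 10^5 or more |
| 2×10^5 | 2×10^5 | 1 | dual, both at 10^5 or more |

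For 5×10^4 each, the dual entry fails because neither organism reaches 10^5. Both middle-band entries fail because growth is neither pure nor predominant. The last entry fails because it stops at 10^4.

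**Step 2: locate the gap.** It is a higher count within 10^4–10^5 and a ratio below 8. It includes pairs straddling 10^4, such as 2×10^4 with 5×10^3. Above it there is no gap: if the higher count is at least 10^5, either the lower is at least 10^4 (dual entry) or the ratio exceeds 10 (predominant entry).

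**Step 3: test the reading.** Making the band limits inclusive or exclusive changes only the exact value 10^4. A 1000-fold predominance rule is not what is printed, and it would widen the gap, not close it.

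**Step 4: how much of the band is empty.** The article gives no distribution of counts, so assume, for illustration only, that counts are log-uniform. With log10(8) = 0.903:

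- both organisms at 10^4–10^5: share meeting no entry = 1 − (1 − 0.903)^2 = 0.991;
- one organism at 10^3–10^4, the other at 10^4–10^5: 0.903^2 / 2 = 0.41;
- higher organism at 10^4–10^5, lower anywhere from 10^3 up to it: 0.903 / 1.5 = 0.60.

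**Step 5: relation to the PA-100 cut-off.** Under the same assumption, the log of the higher count is uniform over the band within the gap. The share of gap cultures with an organism at or above 5×10^4 is then 5 − log10(5×10^4) = 5 − 4.699 = 0.30. If the two counts are summed, about 45% reach the cut-off. So some gap samples would be expected to be PA-100 positive, but most would not.

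**The case against.** The strongest objection is that the article only relays an external rule. Its primary objective commits the reference standard to a guide that is not available here. The gap may be in the guide, in which case a new entry would depart from the stated standard. Or it may be a slip in condensing, in which case the guide still governs the laboratory. This stands: the overlapping entries are a reason to check, and a reader might infer a transcription error, but the document does not establish one. It does not remove the point, because the article prints bands, organism numbers and white-cell conditions as its operative criteria, and these do not fit together.

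Second, the primary analysis is unaffected. This also stands. A reader might infer that the headline accuracy estimates are at risk. They are not, because probable UTI requires pure growth and excludes every two-organism culture whether or not the gap is filled.

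Third, the same section allows a European threshold of 10^3 CFU/mL or more, which could pick up these samples, and the article admits that discordant results may be hard to interpret. The threshold is only an option, so it does not close the gap. The admission does count against any claim that the sensitivity analysis becomes uninterpretable, which would be too strong.

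Fourth, mixed growth at 10^4–10^5 might reflect contamination. That argument would apply at least as much to two organisms at 10^3–10^4, which the rule accepts.

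Finally, a reader might want to state a loss of specificity in percentage points. That needs the share of participants in the gap, the POCT positivity among them and the number of reference negatives. The document gives none of these.

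**Conclusion.** The point holds in a limited form. As printed, the possible-UTI criteria are not monotone in count. With white cells present, two known urinary pathogens with a higher count of 10^4–10^5 and less than 8-fold apart meet no criterion, although lower and higher pairs do. One of the two middle-band entries is redundant.

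The article does not say how cultures that meet no entry are scored; reference negative is the natural inference. On that inference the effect is confined to the possible-UTI sensitivity analysis, where correct detections in the gap would count as false positives. Its size cannot be estimated from the document. The shares in the working describe the shape of the rule under an assumed log-uniform distribution, not the study population. Whether the gap comes from the guide or from its transcription cannot be judged.

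**What to change.** Before any analysis, compare the printed list with the cited guide and set out possible UTI as a table covering every combination of count band, number of organisms and white-cell result, with the outcome stated in each cell. The article says that the SAP will be finalised before any analysis, so it is a natural place for the table.

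- If the redundant middle-band entry is a transcription slip, correct it from the guide.
- If the gap is in the guide, keep the guide's definition, state how such samples are scored, and prespecify one additional analysis. It would count as possible UTI two known urinary pathogens with white cells and a higher count of 10^4–10^5, including pairs straddling 10^4.

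The cost is a wording change and a recode of quantitative counts already recorded, with no new samples or laboratory work. A few more samples become possible UTI, or one more analysis is run. Settling it beforehand avoids a reclassification that would look post hoc once POCT results are known.
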